**6.- STATISTICS**

**6.1 SAMPLE SIZE**

It was estimated that 60 patients (30 in each arm) were needed to detect as significant (two-tailed type I error of 0.05 and a type II error of 0.2) an absolute difference of 25% in the primary endpoint between the groups: 35% in the control group and 10% in the intervention group. Assuming a loss to follow-up of 20%, it is necessary to recruit a total of 72 patients.

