**6.2 STATISTICAL ANALYSIS**

Initially, univariate descriptive analysis will be performed: calculating measures of central tendency and dispersion (means, standard deviation and confidence intervals or median and interquartile range depending on the distribution of the data) for continuous variables and frequencies for qualitative variables with their corresponding confidence intervals for the overall rates. Kolgomorov-Smirnov tests will be used to assess whether the continuous data follow a normal distribution and therefore parametric tests can be used.

Subsequently, it will be assessed whether randomisation achieved balance between the two arms: comparing the means of quantitative variables using Student’s t or the Mann-Whitney U tests, as appropriate, and qualitative variables using the chi-squared test or Fisher´s exact tests. If the desired balance is achieved, the primary endpoint will be compared between the groups to test the null hypothesis (H0) that the proportions are equal, assuming that the statistic for assessing the differences follows a normal distribution with a mean of 0 and standard deviation of 1; otherwise, multivariate analysis will be performed using logistic regression to assess the risk of treatment failure, estimating the effect of the intervention as an odds ratio with the corresponding 95% confidence interval.

The analysis will be performed on an intention-to-treat basis

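### Thirty patients per arm give about 65% power for 35% versus 10%, not the stated 80%, and 72 recruits with 20% loss leave 57.6 patients, not 60

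*Protocol*

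**What the plan says.** Section 6.1 of the protocol gives every input to the calculation. The number and the significance level are set by "It was estimated that 60 patients (30 in each arm) were needed to detect as significant (two-tailed type I error of 0.05", paired with "a type II error of 0.2". The effect is "an absolute difference of 25% in the primary endpoint between the groups", made up of "35% in the control group and 10% in the intervention group". The allowance for loss follows: "Assuming a loss to follow-up of 20%, it is necessary to recruit a total of 72 patients".

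Section 6.2 says how the primary comparison will be tested: equality of the two proportions, "assuming that the statistic for assessing the differences follows a normal distribution with a mean of 0 and standard deviation of 1". That is the ordinary z-test for two proportions. Logistic regression is used instead only if the arms turn out to be unbalanced at baseline. Section 4.3 ends recruitment when the fixed sample size is reached.

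**The concern.** A fall from 35% to 10% is a large effect, but 30 per arm is small even for that. A quick check with the standard formula gives a figure above 40. The step from 60 to 72 also looks like adding 20% to the target rather than dividing by the fraction expected to remain.

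The type II error is the only justification the protocol gives for its size. If it is really about 0.35, a true 25-point benefit would be missed in more than one trial in three at the stated 60 patients, while readers of a null result would assume one in five.

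**Working it through.** **Inputs, all from section 6.1:** p₁ = 0.35, p₂ = 0.10, difference 0.25, two-sided α = 0.05 (z = 1.96), power 0.80 (z = 0.8416), 1:1 allocation. The test is the z-test of section 6.2. The mean proportion is (0.35 + 0.10)/2 = 0.225.

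**1. Trying to reproduce 30 per arm.** The pooled formula is

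n = [1.96·√(2 × 0.225 × 0.775) + 0.8416·√(0.35 × 0.65 + 0.10 × 0.90)]² / 0.25²

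= [1.96 × 0.5906 + 0.8416 × 0.5635]² / 0.0625

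= [1.1575 + 0.4742]² / 0.0625 = 42.6, so 43 per arm (86 in total).

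Other formulas with the same inputs:

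| Formula | Two-sided 0.05, n per arm | One-sided 0.05, n per arm |
|---|---|---|
| Unpooled variance | 39.9 → 40 | 31.4 → 32 |
| Arcsine | 40.5 → 41 | 31.9 → 32 |
| Pooled variance | 42.6 → 43 | 33.4 → 34 |
| Continuity-corrected | 50.3 → 51 | 42 |

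For example, the unpooled figure is (1.96 + 0.8416)² × 0.3175 / 0.0625 = 39.9. No two-sided formula gives 30. The one-sided ones do not reach 30 either, and they contradict the stated two-tailed test. The pooled formula returns 30 only if the test is one-sided and power is also lowered to 75%, which contradicts two of the stated inputs.

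**2. Power actually available.** Rearranging the pooled formula, power = Φ[(0.25·√n − 1.1575)/0.5635].

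- n = 30: (1.3693 − 1.1575)/0.5635 = 0.376, so power = 0.647.
- n = 28.8: (1.3416 − 1.1575)/0.5635 = 0.327, so power = 0.628.
- n = 36: (1.5000 − 1.1575)/0.5635 = 0.608, so power = 0.728.

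Exact enumeration of the pooled z-test over all binomial outcomes gives 0.661 at 30 per arm and 0.743 at 36 per arm. At 30 per arm the unpooled and arcsine approximations give 0.681 and 0.674. None is near 0.80.

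**3. Effect that 30 per arm can detect with 80% power.** Holding control at 35%, the pooled formula returns 30 per arm when the experimental rate is about 6.3%. The difference is then 35 − 6.3 ≈ 29 points instead of 25.

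**4. Loss to follow-up.** The protocol's 72 is reproduced by 60 × 1.2. If 20% of recruits are lost, keeping 60 requires 60/0.8 = 75. Recruiting 72 leaves 72 × 0.8 = 57.6, or 28.8 per arm, which is the 0.628 case above. Put the other way, 72 falls to 60 only if the loss is 12/72 = 16.7%.

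**The case against.** Nothing in the document defends 30 per arm: all the inputs are printed, and no other section gives a different rate, α or formula. The reasonable objections concern size.

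- **Analysed number.** Section 6.2 specifies an intention-to-treat analysis, and section 4.3 has discharged patients followed by telephone. Loss on a 14-day composite of death, ICU admission, ventilation or worsening could be well below 20%. If all 72 are analysed, power is 73–74% and the type II error is about 0.26–0.27. This stands as a reason to quote a range, but it still leaves power short of 80%.
- **Loss arithmetic.** The gap between 72 and 75 is three patients, and it moves power only from 0.647 to 0.628. Alone it would be a minor point, and it should rank below the power error.
- **Regression fallback.** Adjustment could in principle change power, but section 6.2 uses it only after imbalance, and section 6.1 claims no gain from it. It cannot explain the number.
- **Timing.** The appendix reports 46 patients already recruited, so this is a correction to a description rather than to conduct. That keeps the remedy cheap, but the stated type II error remains untrue.

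**Conclusion.** The sample size statement is wrong on its own inputs. For 35% versus 10% at two-sided 0.05, 80% power needs about 43 per arm (40 to 51 depending on the formula), against the stated 30. Power is about 65–66% with 60 patients analysed, about 63% with the 57.6 that 72 recruits leave after 20% loss, and 73–74% if all 72 are analysed. The type II error therefore lies between about 0.26 and 0.37, not at 0.2. The step from 60 to 72 is a second, smaller error.

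These figures assume that the planned rates hold, that allocation is 1:1, and that the primary test is the two-sided z-test of section 6.2, without adjustment for the age strata. The conclusion does not depend on the choice among the usual two-sided formulas.

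**What to change.** Restate section 6.1 so that it is true for the size planned:

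- 30 analysed patients per arm give about 65% power for 35% versus 10% at two-tailed 0.05. Equivalently, they give 80% power only for about 35% versus 6%.
- Give the neighbouring cases: about 63% with 57–58 analysed, and about 73% if all 72 are analysed. Name the formula used.
- Either correct the recruitment figure to 60/0.8 = 75, or keep 72 and state that 20% loss leaves 57–58 patients.

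It would also help, though the correction does not depend on it, to say that a non-significant result will be read from the 95% confidence interval of the risk difference rather than from the planned power.

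The cost is protocol wording and a less favourable power statement, with no extra enrolment if 72 is kept. For comparison, holding to 80% power for 35% versus 10% would need 86 analysed patients and 86/0.8 = 107.5, so 108 recruits.

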**6.2 STATISTICAL ANALYSIS**

Initially, univariate descriptive analysis will be performed: calculating measures of central tendency and dispersion (means, standard deviation and confidence intervals or median and interquartile range depending on the distribution of the data) for continuous variables and frequencies for qualitative variables with their corresponding confidence intervals for the overall rates. Kolgomorov-Smirnov tests will be used to assess whether the continuous data follow a normal distribution and therefore parametric tests can be used.

Subsequently, it will be assessed whether randomisation achieved balance between the two arms: comparing the means of quantitative variables using Student’s t or the Mann-Whitney U tests, as appropriate, and qualitative variables using the chi-squared test or Fisher´s exact tests. If the desired balance is achieved, the primary endpoint will be compared between the groups to test the null hypothesis (H0) that the proportions are equal, assuming that the statistic for assessing the differences follows a normal distribution with a mean of 0 and standard deviation of 1; otherwise, multivariate analysis will be performed using logistic regression to assess the risk of treatment failure, estimating the effect of the intervention as an odds ratio with the corresponding 95% confidence interval.

The analysis will be performed on an intention-to-treat basis

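### Baseline significance tests choose the primary analysis, so its test and effect measure are not fixed in advance

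*Protocol*

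**What the plan says.** Protocol section 6.2 sets out a sequence. After descriptive statistics, "it will be assessed whether randomisation achieved balance between the two arms". Quantitative variables are compared by Student's t or Mann-Whitney tests, and "qualitative variables using the chi-squared test or" Fisher's exact test.

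The outcome of that step picks the primary analysis. On one route, "If the desired balance is achieved, the primary endpoint will be compared between the groups to test the null hypothesis" of equal proportions, using a statistic taken as standard normal; no effect measure is named. On the other, "otherwise, multivariate analysis will be performed using logistic regression to assess the risk of treatment failure", with the effect given as an odds ratio and 95% confidence interval.

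The section does not say which variables are tested, at what threshold, how many differences count as imbalance, or which covariates enter the model. It closes by saying that the analysis is by intention to treat, which fixes the population but not the method. Section 5.2 stratifies randomisation by age (under 75, 75 and over); neither route mentions that factor.

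**The concern.** The sequence is generated by a unit independent of recruitment (section 5.2). If it is carried out as described, every baseline difference between the arms is due to chance. A small p-value for such a difference does not show whether the variable predicts treatment failure, so it is a poor guide to whether adjustment is worthwhile.

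The two routes also report different things. The sample size in section 6.1 rests on an absolute difference in proportions. The unadjusted route tests equality of proportions without naming a measure. The logistic route reports an odds ratio conditional on the covariates in the model, which changes with the covariates even when the data do not. Chance imbalance, together with a judgement about what counts as adequate balance, would decide which of these is the trial's primary result.

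**Working it through.** **Inputs.** Section 6.1: "two-tailed type I error of 0.05 and a type II error of 0.2", "35% in the control group and 10% in the intervention group", "60 patients (30 in each arm) were needed", and 72 recruited. Section 5, independent variables, baseline items only: 2 epidemiological + 13 comorbidity + 2 dates + 9 home medication + 11 baseline blood tests + 3 radiological = 40. In-hospital medication, follow-up tests and safety events are left out.

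**The plan's own figure.** The protocol gives no figure for the balance step. Its sample size does not reproduce: the pooled two-sided formula gives (1.960·√(2·0.225·0.775) + 0.842·√(0.35·0.65 + 0.10·0.90))² / 0.25² = 42.6, so 43 per arm, and power at 30 per arm is about 65%. That is a separate issue and nothing below depends on it. It only explains why the plain test starts near 65% rather than 80%.

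**How often each route is taken.** Assume k variables are tested at 0.05 and one significant result triggers the switch. With independent tests, P(unadjusted route) = 0.95^k.

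| Variables tested | P(unadjusted route) |
|---|---|
| 5 | 77.4% |
| 10 | 59.9% |
| 20 | 35.8% |
| 40 | 12.9% |

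A simulation of all 40 items used 18 continuous or ordinal variables (t-test) and 22 binary variables (chi-squared, or Fisher where expected counts fall below 5). Prevalences of 3% to 70% were assumed, with 3,000 runs per setting.

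| Common correlation | 30 per arm | 36 per arm |
|---|---|---|
| 0 | 24.4% | 21.5% |
| 0.2 | 29.3% | 26.8% |
| 0.4 | 35.9% | 37.3% |

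So with all 40 tested, the range is about 13% (independent tests of exact size) to 37% (discrete, correlated variables).

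**Difference in scale.** At the design rates the risk difference is 0.35 − 0.10 = 0.25. The unadjusted odds ratio is (0.10/0.90)/(0.35/0.65) = 0.21, and an adjusted odds ratio is a further, covariate-dependent quantity.

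**Events available to the model.** With 60 patients: 30·0.35 + 30·0.10 = 13.5. With 72: 36·0.35 + 36·0.10 = 16.2. Either supports very few covariates.

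**Power.** This assumes that the model adjusts for each variable with p < 0.05 at baseline. Simulations used independent covariates, some of them prognostic; the second row for 38 variables and the row for 40 come from separate simulations with their own assumed covariate effects.

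| Variables tested (prognostic) | Per arm | Two-step rule | Plain z-test | Loss, points |
|---|---|---|---|---|
| 5 (3) | 30 | 64% | 67% | 3 |
| 10 (5) | 30 | 61% | 66% | 5 |
| 10 (5) | 36 | 72% | 76% | 4 |
| 38 (5) | 30 | 52% | 66% | 14 |
| 38 (5) | 30 | 54% | 65% | 11 |
| 40 (3) | 30 | 55% | 69% | 14 |

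In the 40-variable simulation the two-step rule and the plain test disagreed about significance in 20.6% of trials with a large effect and in 3.7% of null trials.

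**Type I error.** Applied mechanically, the two-step rule rejected in 4.8% of null trials against 5.4% for the plain test (40 variables), and in 4.4% against 5.0% in a separate simulation with 38. If an analyst could take whichever route was significant, the 40-variable figure would be 6.9%.

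**The case against.** The strongest reply is that the size of the problem rests on choices the protocol does not state. Section 5 is a data-collection list; nothing says that every item is balance-tested, that 0.05 is the threshold, or that one difference is enough. Many items are plainly related: smoker and ex-smoker, diabetes and its drugs, the Charlson index and its components, the inflammatory markers. Age is partly controlled by stratification. The trigger and the covariates could also be defined in a statistical analysis plan that is not at hand.

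Most of this stands, and it rules out several stronger readings that a reader might infer:

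- That the unadjusted test would rarely be used. This needs all 40 variables, independence, a 0.05 threshold and a single-hit trigger. With short lists the unadjusted route is the usual one.
- That the plan adjusts for whatever differs and so loses power. No covariate rule is stated, so the loss is conditional on an assumption and is only a few points for short lists.
- That false positives are inflated. The simulations do not show this when the rule is followed mechanically.
- That the rule switches away from a planned risk difference. The unadjusted route names no effect measure.

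The objection does not remove the rule itself. The protocol does not merely leave the choice open; it says that baseline comparisons make it. An analysis plan could define the trigger, but fixing a single analysis would contradict section 6.2.

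**Conclusion.** The point holds as a defect in how the primary analysis is fixed. Section 6.2 makes both the test and the effect measure depend on chance baseline differences and on an undefined judgement of balance, and no other section settles the matter.

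The size can be given only as a range. The unadjusted route would be taken in about 13% to 37% of trials if all 40 items were tested at 0.05 with a single-hit trigger, and in about 60% or 77% with 10 or 5 independent variables. Power would fall by about 3 to 5 points with 5 to 10 variables tested and by about 11 to 14 with 38 to 40, if the model adjusts for what differs. The harm is an analysis and estimand not fixed in advance, with room for discretion between routes and a possible loss of power. The correction is warranted on those grounds, whatever the power figures turn out to be.

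**What to change.** Delete the balance-test branch. By a dated amendment, made blind to allocation and before unblinding, fix one primary analysis that applies whatever the baseline table shows: the between-arm risk difference in treatment failure to day 14, with 95% confidence interval and p-value, by intention to treat, stratified by the randomisation factor (age under 75, 75 and over), for example by Mantel-Haenszel. Show baseline data descriptively, without p-values. Keep logistic regression as a sensitivity analysis with at most a few covariates named in advance; 13.5 to 16.2 expected events allow no more.

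No new data or patients are needed, but this is more than a rewording. The protocol's appendix reports 46 patients recruited and analysis under way, which is past the halfway point of 72 (36) at which section 4.3 places the interim analysis. The amendment should therefore state what had been seen when it was made, and any analysis already run under the present rule should be disclosed alongside the new one.

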**Exclusion criteria:**

- Allergy or contraindication to the drugs under study
- Signs of respiratory failure: SpO_2_ in ambient air < 90% or PaO_2_ in ambient air < 60 mmHg or PaO_2_/FiO_2_ < 300 mmHg
- Need for glucocorticoids or other immunosuppressants (including biologics) for another indication
- Decompensated diabetes mellitus
- Uncontrolled hypertension
- Psychotic or manic disorder
- Active cancer
- Pregnancy or breastfeeding
- Clinical or biochemical (procalcitonin > 0.5 ng/mL) suspicion of active infection with any pathogen other than SARS-CoV-2
- Management as an outpatient
- Conservative or palliative management
- Participation another clinical trial
- Any other major uncontrolled medical, psychological, psychiatric, geographic, or social problem contraindicating patient’s participation in the study or that hinders proper patient follow-up and adherence to the protocol and the evaluation of study outcomes.

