**5.4 FOLLOW-UP METHODS**

**5.4.1 Baseline assessment**

All the patients included in the study will be assessed at baseline in the emergency department or on the hospital ward. This baseline assessment will include the following elements:

- Guided clinical history
- Medical history and comorbidities
- Concomitant treatments
- Vital signs: temperature, blood pressure, heart rate, respiratory rate and oxygen saturation
- Physical examination
- Blood tests: blood count, coagulation tests including D-dimer, renal function, and levels of CRP, procalcitonin, ferritin, LDH and IL-6
- Chest X-ray (interpreted by a pulmonary radiologist).

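### Baseline oxygen saturation is recorded in every patient and lies on the scale of one failure criterion, but the default primary test ignores it; always adjusting could gain roughly 1 to 10 points of power, depending on a correlation the protocol does not give

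*Protocol*

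**What the plan says.** **Primary analysis (Protocol 6.2).** The arms are first compared at baseline with t, Mann-Whitney, chi-squared or Fisher tests. If balance is judged adequate, "the primary endpoint will be compared between the groups to test the null hypothesis (H0) that the proportions are equal", using a standard normal statistic and no covariates. Otherwise a logistic regression is fitted and an odds ratio reported. No significance level for the balance tests is given.

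**Baseline data (5.4.1).** "All the patients included in the study will be assessed at baseline in the emergency department or on the hospital ward". The items include "Vital signs: temperature, blood pressure, heart rate, respiratory rate and oxygen saturation". The list of independent variables also has a baseline SpO2/FiO2.

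**Entry and failure.** The exclusion headed "Signs of respiratory failure" (4.4) removes patients with ambient-air SpO2 below 90%, PaO2 below 60 mmHg or PaO2/FiO2 below 300 mmHg. Under Primary Endpoint, reaching any of these three limits by day 14 counts as failure. So do death, ICU admission, mechanical ventilation, and a PaO2 fall of at least 15% with laboratory or radiological progression.

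**Randomisation (5.2).** Stratified by age below or above 75 years, not by oxygenation.

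**Size (6.1).** "60 patients (30 in each arm) were needed to detect as significant" a difference of "35% in the control group and 10% in the intervention group", with "two-tailed type I error of 0.05 and a type II error of 0.2".

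**The concern.** On the SpO2 route, entry limit and failure line are the same number. A patient who enters at 90% fails after a drop of one point; one who enters at 97% must drop eight. Baseline saturation is the starting distance from failure on that route, so it is a natural covariate.

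The default test leaves it out. Two things are at stake. The first is precision in a small trial: with 30 per arm the plan expects 30 × 0.35 + 30 × 0.10 = 13.5 failures. The second is chance imbalance. Randomisation does not stratify on oxygenation, and a balance test at this size misses differences that can matter. Because the balance result also selects the primary analysis, the data decide which test is run.

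**Working it through.** **1. The plan's own size.** Inputs from 6.1: p0 = 0.35, p1 = 0.10, mean 0.225, two-sided 0.05, power 0.80.

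n per arm = [1.96·√(2·0.225·0.775) + 0.8416·√(0.35·0.65 + 0.10·0.90)]² / 0.25² = (1.1575 + 0.4742)² / 0.0625 = 42.6, so 43.

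The stated 30 is not reproduced. Power at 30 per arm:

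Φ[(0.25 − 1.96·√(0.34875/30)) / √(0.3175/30)] = Φ[(0.25 − 0.2113)/0.1029] = Φ(0.376) = 64.7%.

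Arcsine and unpooled versions give 67 to 68%. This shortfall is a separate matter; here it sets the starting point at about 65 to 67%, not 80%.

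**2. Analytic gain.** If adjustment cuts the variance of the effect by a fraction R, the effective size is 30/(1 − R). R is not in the protocol. Below it is derived from an assumed odds ratio per SD of baseline saturation, then put into the power formula above.

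| Assumed OR per SD | R | Effective n per arm | Power | Gain (points) |
|---|---|---|---|---|
| 1.5 | 2.5% | 30.8 | 65.8% | about 1 |
| 2 | 6.7% | 32.2 | 67.8% | about 3 |
| 2.5 | 10.8% | 33.6 | 69.8% | about 5 |
| 3 | 14.3% | 35.0 | 71.6% | about 7 |
| 4 | 19.9% | 37.5 | 74.6% | about 10 |

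**3. Simulated gain.** Failure comes from a latent normal variable with an assumed correlation to baseline saturation; marginal rates are 35% and 10%, 30 per arm, 4,000 trials per setting. The pooled z-test is compared with the score test from a logistic model including saturation. Ranges are from two independent runs.

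| Correlation | z-test | Adjusted | Gain (points) |
|---|---|---|---|
| 0 | 66.8% | 67.2% | 0.4 |
| 0.2 | 67.0% | 68.7% | 1.7 |
| 0.3 | 66.2–67.0% | 69.0–69.5% | 2.5–2.8 |
| 0.4 | 66.2% | 69.9% | 3.7 |
| 0.5 | 65.8–66.8% | 72.2–73.8% | 6.4–7.0 |
| 0.6 | 65.4–67.2% | 75.9–77.6% | 10.4–10.5 |

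The Monte Carlo standard error of each power is √(0.67·0.33/4000) = 0.7 points. Adding the age stratum gives gains of about 0, 1.5, 2, 7 and 10 points at 0, 0.2, 0.3, 0.5 and 0.6. At 36 per arm (no losses) and 0.5, power goes from 73.6–75.4% to 80.0–81.5%.

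**4. Type I error.** The model with saturation and age stratum rejects 5.6 to 5.8% under the null, against 4.1 to 5.3% for the z-test. Calibrating the saturation-only score test to 5% (8,000 trials) leaves 66.1% v 65.5% at 0.3, 69.2% v 65.6% at 0.4 and 72.8% v 67.3% at 0.5: gains of 0.6, 3.6 and 5.5 points. The likelihood-ratio test is more liberal (5.6 to 6.3%, null at 35% in both arms).

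**5. Does the balance check protect the comparison?** Take a chance difference of 0.5 SD in baseline saturation. Then t = 0.5/√(2/30) = 1.94, p ≈ 0.06, which passes a balance test at an assumed 5% level. With no treatment effect and correlation 0.5, the z-test then rejects 9.3% of the time and the adjusted score test 5.7%. At 0.4 SD the figures are 7.1% and 5.5%. These rates are conditional on that imbalance; they are not the overall type I error.

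**The case against.** **The unadjusted test is valid.** This stands. Averaged over randomisations its size is close to 5%, and nothing in the protocol contradicts it. The point concerns efficiency and a poor rule for choosing the analysis, not validity.

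**A fixed loss of about 7 points.** A reader might infer this from the shared 90% cut-off. The documents do not support it: they give no prognostic strength, and 7 points needs a correlation near 0.5 or an odds ratio near 3 per SD.

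**The association may be weak.** This also stands. Entry at SpO2 of 90% or more narrows the covariate, while the simulations use an untruncated normal. Patients can fail by other routes, and the 15% PaO2 criterion is relative to the patient's own baseline. The share failing through SpO2 is not stated.

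**The recorded value may not be an ambient-air one.** 5.4.1 does not say. Applying the SpO2 exclusion does require an ambient-air value, so one should exist, but this is an inference.

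**Covariate lists belong in the SAP.** True of the fallback model, whose unnamed covariates are not criticised here. But 6.2 itself fixes an unadjusted default and the condition for leaving it.

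**Few events.** Some 13 to 14 failures for arm, saturation and age stratum is 4 to 5 per parameter, and part of the apparent gain is liberality. Both temper the benefit without removing it.

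**Conclusion.** The concern holds as a conditional one. The protocol sets aside a baseline value measured in everyone, on the scale and cut-off of one failure criterion, and lets baseline significance tests decide whether any adjustment is made.

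At 30 per arm and 35% versus 10%, always adjusting would gain roughly 1 to 10 points of power over assumed correlations of 0.2 to 0.6: about 1 to 3 at 0.3 and about 5 to 7 at 0.5, from about 65 to 67%. Part of this reflects null rejection of about 5.5 to 6%. Even a 10-point gain would not bring 30 per arm to the stated 80%, so adjustment is no cure for the sample size. The change should be made because it costs almost nothing if the covariate proves weak.

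**What to change.** In Protocol 6.2:

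- Remove the balance tests as the condition that selects the primary analysis; describe baseline data without letting them choose the test.
- Pre-specify in all cases a logistic regression of treatment failure on arm, baseline SpO2 (continuous, the ambient-air value needed for eligibility) and the age stratum.
- Use the score test, since the likelihood-ratio test is more liberal here.
- Report the standardised risk difference with 95% CI beside the odds ratio, and keep the unadjusted difference in proportions as supportive.

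In 5.4.1, state that the baseline saturation is taken in ambient air.

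**Cost.** Wording only, if the eligibility value is recorded. The downsides are few events per parameter and slight type I inflation. The appendix notes that 46 patients had been recruited and analysis was under way. If unblinded outcomes have already been seen, the adjusted model can no longer count as pre-specified and should be reported as a sensitivity analysis.

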**5.- OUTCOME MEASURES**

5.1 PRIMARY ENDPOINT

Proportion of patients with treatment failure up to 14 days after randomisation.

Definition of treatment failure:

1. Patient death or
2. ICU admission or
3. Start of mechanical ventilation or
4. Clinical worsening, defined as:
   - Decrease in PaO_2_ by ≥15% from baseline + laboratory or radiological progression or
   - SpO_2_ in ambient air falling to < 90% or PaO_2_ in ambient air to < 60 mmHg or PaO_2_/FiO_2_ < 300 mmHg.

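### The fallback primary analysis in section 6.2 is a multivariable logistic odds ratio with no covariate limit, resting on about 13 to 16 expected failures; Firth's penalised likelihood and a short covariate list should be specified

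*Protocol*

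**What the plan says.** The primary endpoint (protocol section 5.1) is binary: "Proportion of patients with treatment failure up to 14 days after randomisation". Section 6.1 sizes the trial as a comparison of two proportions, for "an absolute difference of 25% in the primary endpoint between the groups: 35% in the control group and 10% in the intervention group", with "two-tailed type I error of 0.05 and a type II error of 0.2". It concludes that "60 patients (30 in each arm) were needed", and then: "Assuming a loss to follow-up of 20%, it is necessary to recruit a total of 72 patients".

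Section 6.2 gives the primary analysis two branches. If baseline comparisons show the arms to be balanced, the proportions are compared with a z-test, "assuming that the statistic for assessing the differences follows a normal distribution with a mean of 0 and standard deviation of 1". If not, the second branch applies: "otherwise, multivariate analysis will be performed using logistic regression to assess the risk of treatment failure, estimating the effect of the intervention as an odds" (an odds ratio, reported with a 95% confidence interval). The section does not name the covariates or limit their number. It does not name the estimator or the type of test and interval, and it does not say what is reported if an arm has no failures.

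**The concern.** A multivariable odds ratio needs a reasonable number of events for each coefficient, and this trial expects few. Three things can go wrong with an ordinary fit:

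- The odds ratio tends to be too far from 1, and more so with each covariate added.
- If no patient in the active arm fails, the odds ratio has no usable value or Wald interval. This would be the most favourable result the drug could produce.
- The test may not perform like the z-test on which the trial was sized.

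These problems arise however the logistic branch is entered. They are separate from the question of whether baseline tests should choose the branch at all.

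**Working it through.** **Inputs (section 6.1).** Failure risks 0.35 (control) and 0.10 (active), two-sided 0.05, type II error 0.2, 30 per arm evaluable, 72 recruited (36 per arm).

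**The plan's own sample size.** The pooled two-proportion formula, with mean risk 0.225, gives

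n = [1.960·√(2·0.225·0.775) + 0.842·√(0.35·0.65 + 0.10·0.90)]² / 0.25² = 42.6, so 43 per arm.

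The stated 30 per arm is not reproduced. Exact power of the pooled z-test at 30 per arm is 66.1%, and that is the benchmark here. The 72 equals 60 × 1.2; dividing by the retained fraction gives 60/0.8 = 75. The shortfall in sample size is a separate matter.

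**Expected failures.**
- 30 per arm: 30 × 0.35 + 30 × 0.10 = 10.5 + 3.0 = 13.5
- 72 less 20%, i.e. 57.6 patients: 28.8 × 0.45 = 13.0
- All 72 analysed: 36 × 0.45 = 16.2, of which 3.6 in the active arm

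**True effect.** Odds ratio = (0.10/0.90)/(0.35/0.65) = 0.206; log odds ratio −1.578.

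**No failures in the active arm.** 0.9³⁰ = 4.2%; 0.9³⁶ = 2.3%. Take 0/30 against 10/30. The pooled z is 0.333/√(2·0.1667·0.8333/30) = 3.46, clearly significant. The maximum-likelihood odds ratio is 0, its log is minus infinity, and no Wald interval exists. Firth's method without covariates amounts to adding 0.5 to each cell and gives (0.5/30.5)/(10.5/20.5) = 0.032, which is finite.

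**Bias without covariates (exact enumeration of all tables, finite estimates only).** At 30 per arm the mean log odds ratio is −1.639 against −1.578. The ratio is 1.039, about 4% too large, and corresponds to an odds ratio of 0.194.

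**Bias with covariates (simulation, 30 per arm).** The excess on the log scale is 5–7% with one standard-normal covariate, 12–15% with three and 17–28% with five. A second simulation assumed covariates with no prognostic effect, half normal and half binary with 20% prevalence. With 2, 4 and 6 of them the median odds ratio is 0.18, 0.17 and 0.15, and some coefficient diverges in about 10%, 16% and 20% of trials.

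**Tests without covariates (exact enumeration; zero-cell tables count as not significant by Wald).**

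| Per arm | z power | Wald power | Likelihood-ratio power |
|---|---|---|---|
| 29 | 64.2% | 56.2% | 68.0% |
| 30 | 66.1% | 57.8% | 69.7% |
| 36 | 74.3% | 71.1% | 76.3% |

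The Wald loss is 8.0, 8.3 and 3.2 points. About 4.2 of the 8.3 points at 30 per arm are the no-failure tables. The rest come from tables such as 1/30 against 6/30, where z = 2.01 but Wald = 1.98/1.115 = 1.78. In simulation at 30 per arm the Wald loss is about 7–8 points with non-prognostic covariates and about 2–4 with prognostic ones.

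Type I error at a common risk of 22.5%, 30 per arm: z 4.9%, Wald 3.7%, likelihood ratio 6.0% (5.6% at 36 per arm).

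**Firth with a penalised likelihood-ratio test (simulation).** Power at 30 per arm is about 66% without covariates and 61–68% with one to five; at 36 per arm it is 70–76%. Type I error is about 4–6%. The geometric-mean odds ratio is 0.203–0.204, and the estimate is always finite. A Firth estimate with a Wald test recovers no power (about 59% at 30 per arm), so the profile test has to be specified too.

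**The case against.** The strongest reply is that the protocol does not specify what is being criticised. It says logistic regression, odds ratio and confidence interval. Maximum likelihood, Wald and the handling of empty cells are left open, and a statistical analysis plan that is not shown may settle them. This stands to the extent that every figure above is conditional on the default implementation. It does not dispose of the point: the protocol itself commits a branch of the primary analysis to a multivariable odds ratio without a covariate limit, at an event count its own rates show to be small.

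A reader might infer that a maximum-likelihood odds ratio as such costs 8 points of power. The documents and the calculations do not support this. The loss belongs to a Wald test, at about 30 per arm, without prognostic covariates. It is about 3 points if all 72 patients are analysed, which the intention-to-treat statement would favour. It disappears with a likelihood-ratio test on the same fit, although that test exceeds the nominal 5%.

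A reader might also infer that the most favourable result could never be declared significant. That holds only if the p-value comes from a Wald test. The chance of an empty active arm is 2 to 4%, and it matters only if the logistic branch is used.

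Finally, the bias is small without covariates, and the undersized trial and the choice of analysis by baseline tests are larger problems. Both statements are right. Neither removes the estimation problem wherever logistic regression is used.

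**Conclusion.** The point holds as an inexpensive improvement to a poorly fixed primary method. It does not show that the plan prescribes a wrong test. With 13 to 16 expected failures and no covariate limit, a default maximum-likelihood fit would exaggerate the effect by about 4% on the log scale without covariates and by more than 10% with three or more. It would give no finite odds ratio in 4.2% of trials at 30 per arm (2.3% at 36). Of the two usual tests, Wald loses power (8 points at 30 per arm, about 3 at 36, about 2–4 at 30 per arm with prognostic covariates), and the likelihood-ratio test has type I error of about 6%.

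These figures assume the planned 35% and 10%. Those with covariates also depend on the assumed number, distribution and prognostic strength of the covariates, none of which the protocol gives.

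**What to change.** In section 6.2, replace the logistic sentence with wording such as: *Any logistic model for the primary endpoint will be fitted by Firth's penalised likelihood. The p-value and 95% confidence interval will come from the profile penalised likelihood. The model will contain treatment, the age stratum used in randomisation (<75, ≥75 years) and at most one other covariate named in advance. The model-standardised risk difference will be reported alongside the odds ratio.*

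The age stratum is already recorded for randomisation (section 5.2), and the risk difference is on the scale used for the sample size. The cost is a change of wording and a standard R routine, with no extra patients or data. The downside is that the odds ratio will be slightly closer to 1 than the maximum-likelihood one, and fewer covariates can be adjusted for.
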